## Abstract

**Background:**

One-year dual antiplatelet therapy (DAPT), generally aspirin in combination with a P2Y12 receptor inhibitor, has been a standard treatment for patients undergoing percutaneous coronary intervention (PCI). Prolonged DAPT has proven itself effective in further reducing cardiovascular events, yet with increased risk of bleeding. Thus, it is of great necessity to find an alternative drug that is as effective but safer and more economic than the P2Y12 inhibitors after termination of one-year DAPT.

**Methods:**

We will conduct a cluster randomized controlled trial in 3600 eligible post-PCI patients from 36 tertiary hospitals (100 patients per hospital) across mainland China. The hospitals served as clusters are randomized in a 2:1 ratio to Guanxinning tablet (GXNT) plus aspirin or aspirin alone for 12 months, with other conventional treatment applied in both groups. After the treatment period, all patients will be followed up for another 12 months. The primary outcome measure is composite cardiovascular events including cardiovascular death, non-fatal myocardial infarction, stent thrombosis, revascularization, ischemic stroke, and re-admission due to unstable angina. Secondary outcome measures are all-cause mortality, each individual component of the primary outcome measure, and stopping or reducing the rate of nitroglycerin administration. Adverse events, including bleeding, will be closely monitored during the whole trial period. In addition, a cost-effectiveness study of GXNT for the study population will be conducted along with this trial.

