### Inclusion criteria

To be eligible to participate in the trial, patients should:Be currently stable (without angina or with stable angina, defined as persistent and reproducible chest discomfort caused by myocardial ischemia and precipitated by a physical exertion that dissipates upon cessation of such an activity, within the last 3 months before screening) and have received standard DAPT (aspirin plus clopidogrel or prasugrel or ticagrelor) for at least 12 months after PCIHave switched from DAPT to aspirin monotherapy for at least one monthBe diagnosed with the blood stasis pattern of traditional Chinese medicine, which is the most common traditional Chinese medicine syndrome of coronary artery disease; patients with any one of the following signs will be diagnosed as having the blood stasis pattern:dark purple or dark red tongue, or petechia or ecchymosisbluish-purple or dark color of the lipsvaricosity or abnormal telangiectasia of the sublingual veins [22]Be between 18 and 80 years of ageProvide written informed consent.

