### Settings and recruitment

Qualified drug clinical trial institutions or tertiary hospitals across mainland China have been invited, and the first 36 hospitals to agree to participate will be included. Each hospital is expected to recruit 100 eligible patients. Patients can be recruited by screening inpatients and outpatients of each hospital, through media advertising and social media or by screening a PCI database. Potential eligible patients will be screened and assessed by trained investigators, and eligible participants will be asked to provide written informed consent.

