### Allocation

Thirty-six participating hospitals (clusters) with 3600 patients are firstly stratified by type of medication delivery (Western medical or traditional Chinese medicine hospitals), and then hospitals in each stratification are randomly allocated in a 2:1 ratio by a computer-generated, centrally controlled randomization schedule to treatment (24 hospitals with 2400 patients) or control (12 hospitals with 1200 patients) arms (see Fig. 1). All patients from one cluster will receive same intervention. Though the patients and caregivers are not blinded, the outcome assessors and data analysts are to be blinded to treatment allocation to minimize potential bias.

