### Outcome measures

The primary efficacy outcome measure is the composite cumulative incidence of MACE, including cardiovascular death, non-fatal myocardial infarction, stent thrombosis, revascularization, ischemic stroke, and re-admission for unstable angina during the treatment and follow-up periods. The secondary efficacy outcome measures are stopping or reducing the rate of nitroglycerin tablets and the respective cumulative incidence of all-cause death, cardiovascular death, non-fatal myocardial infarction, stent thrombosis, revascularization, ischemic stroke, and re-admission for unstable angina. Other efficacy outcomes include hypersensitivity C-reactive protein and platelet aggregation rate. Patients’ costs, the Seattle Angina Questionnaire rating, and health-related quality of life determined by the generic Short Form-36 (SF-36) questionnaire will be additionally assessed for cost-effectiveness analysis.

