### Sample size and data analysis

As little data on MACE rate in post-PCI patients who switch from DAPT to aspirin for about 12 months is available, we have to calculate the sample size according to the results of other studies. One registry trial reported that the annual rate of death or myocardial infarction was approximately 4.7%/year for patients who underwent successful implantation of at least one drug-eluting stent and did not received prolonged DAPT [25]. Another retrospective study indicated that the 2 year composite rate of mortality, reinfarction, and target vessel revascularization for patients undergoing primary PCI after acute myocardial infarction was 23% to 30% [26]. Though participants in our trial may have a lower rate of mortality, reinfarction, and target vessel revascularization than the retrospective study, taking other components into account, including stent thrombosis, ischemic stroke, and re-admission for unstable angina, we estimate the 12 month rate for the primary outcome measure in patients taking aspirin alone might be 21%, and that GXNT will reduce the incidence by 21%. A statistic power of 0.8 and a type I error rate of 0.05 (alpha) are chosen. According to a previous study, we assume the coefficient of intracluster correlation to be 0.002 [27] and we expect to recruit 90 patients from each cluster (hospital). Thus, a total of 3240 patients with 36 clusters (hospitals) will be needed. Considering a dropout rate of 10%, a minimum of 3564 patients is needed; for convenience of randomization, we decided to recruit 3600 patients (100 patients per hospital) and 36 hospitals (2400 patients and 24 clusters in the treatment arm, 1200 patients and 12 clusters in the control arm). Considering the uncertainty of the MACE rates in the study population, an interim analysis will be conducted when one-third of expected MACEs occur and the sample size will be adjusted according to the results of the interim analysis.

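### The primary composite counts any revascularization, and eligibility does not exclude patients whose coronary revascularization is already planned at enrolment

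*Protocol article*

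**What the plan says.** The governing definition is in the article's Outcome measures section. It lists "cardiovascular death, non-fatal myocardial infarction, stent thrombosis, revascularization, ischemic stroke, and re-admission for unstable angina during the treatment and follow-up periods". The Abstract gives the same list, "including cardiovascular death, non-fatal myocardial infarction, stent thrombosis, revascularization, ischemic stroke, and re-admission due to unstable angina", and the Fig. 2 footnote also names revascularization; none of the three says unplanned, or decided after enrolment.

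On who may enter:
- Inclusion criteria: a patient must "Be currently stable (without angina or with stable angina", with at least 12 months of DAPT after PCI and at least one month on aspirin alone.
- Settings and recruitment: "Patients can be recruited by screening inpatients and outpatients of each hospital"; advertising and a PCI database are further sources.
- Exclusion criteria: the items cover heart failure, blood pressure, organ disease and malignancy, bleeding risk, allergy, pregnancy and recent participation in another trial. None covers a planned or scheduled coronary procedure.

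On allocation and blinding, the Allocation section says "All patients from one cluster will receive same intervention" and "Though the patients and caregivers are not blinded, the outcome assessors and data analysts are to be blinded". Data management and monitoring adds an independent, blinded endpoint committee for all MACEs, but states no rule for procedures planned before entry.

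**The concern.** A stable-angina patient who is waiting for an elective coronary procedure passes every listed criterion. When the procedure takes place, it meets the primary endpoint as defined. The decision came before the first tablet, so the event carries no information about GXNT.

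Two consequences follow. If such events are equally common in both arms, they pull the risk ratio towards 1 and cost power. If they are not equally common, they create a difference unrelated to the drug. The second is a realistic worry here because whole hospitals are assigned to one arm and caregivers know which. The article does not say that patients are identified before allocation, so the mix of patients enrolled can depend on the arm. Blinded adjudication does not help: a planned procedure is a true revascularization, and a committee applying the stated definition would be right to count it.

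**Working it through.** **Inputs from Sample size and data analysis:** control rate 21% at 12 months; 21% relative reduction; alpha 0.05 (two-tailed, as the analysis text states); power 0.80; intracluster correlation 0.002; 36 hospitals of 90 evaluable patients, 2:1, hence 1080 control and 2160 GXNT patients.

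**Assumption, not in the article:** a share q of patients has a pre-planned procedure that counts as an event and that GXNT cannot change.

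**Step 1. Reproduce the plan's figure.**
- GXNT rate = 0.21 × 0.79 = 0.1659; difference 0.0441.
- Design effect = 1 + 89 × 0.002 = 1.178. Effective sizes: 1080/1.178 = 916.8 and 2160/1.178 = 1833.6.
- The two-proportion formula (pooled variance under the null, no continuity correction) needs 2736 patients. 2736 × 1.178 = 3223, against the stated 3240.
- Power at 3240: pooled rate (0.21 + 2 × 0.1659)/3 = 0.1806; null SE 0.01556; alternative SE 0.01601. (0.0441 − 1.96 × 0.01556)/0.01601 = 0.85, so power is 80.2%.

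The design reproduces and has almost no slack.

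**Step 2. Equal share q in both arms, same power formula.**
- Model A, planned procedures lie within the 21%: control 0.21; GXNT = q + (0.21 − q) × 0.79.
- Model B, they come on top: control = q + (1 − q) × 0.21; GXNT = q + (1 − q) × 0.1659.

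| q | A: GXNT rate | A: risk ratio | A: power | B: rates, control / GXNT | B: power |
|---|---|---|---|---|---|
| 0 | 0.1659 | 0.790 | 80.2% | 0.2100 / 0.1659 | 80.2% |
| 0.5% | 0.1670 | 0.795 | 78.2% | 0.2140 / 0.1701 | 79.2% |
| 1% | 0.1680 | 0.800 | 76.2% | 0.2179 / 0.1742 | 78.1% |
| 2% | 0.1701 | 0.810 | 71.7% | 0.2258 / 0.1826 | 76.1% |

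**Step 3. Unequal share, no drug effect.** With d the gap between arms and SE the unpooled standard error at the effective sizes, the two-sided rejection rate is Φ(d/SE − 1.96) + Φ(−d/SE − 1.96).
- Control 21%, GXNT 20%: SE 0.01638, rejection 9.4%.
- Control 21%, GXNT 19%: SE 0.01628, rejection 23.3%.
- Reversed, GXNT 22% or 23%: SE 0.01657 or 0.01666, rejection 9.3% or 22.5%, now against GXNT.

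The nominal rate is 5%. A 2-point gap is 2/4.41 = 45% of the targeted difference. These gaps are illustrations only.

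**The case against.** The strongest reply is that this is a condensed article. It gives no operational definition for any component, and the endpoint committee must work from definitions that are not shown, which may set planned procedures aside. That caveat stands. It does not remove the point, because the article does set out its eligibility criteria item by item and does state the composite, and together these admit the patient and count the procedure.

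Second, enrolment comes at least 13 months after PCI, in patients who have been stable for three months and are to stay on aspirin monotherapy. Staged procedures from the index PCI will mostly be over, and a patient booked for a new stent fits this course poorly. Listing inpatients as a source does not mean that they are in hospital for revascularization. This stands too: such patients are probably few, though not excluded.

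Third, the interim sample-size adjustment might recover lost power. It might, but it does nothing about a difference in enrolment between arms.

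A reader might infer more than the documents support:
- That the 80% power is lost. The share is unknown; at 0.5% the loss is two points or less.
- That the bias favours GXNT. Nothing shows that control hospitals would enrol more patients awaiting a procedure, and the reverse is equally possible.
- That the sizing is inconsistent because one source reported a "2 year composite rate of mortality, reinfarction, and target vessel revascularization". Target vessel versus any vessel has no bearing on whether a procedure was planned, and the article says openly that it extrapolates and allows for further components.

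**Conclusion.** The point holds as a weakness in how eligibility and the primary endpoint fit together: as written, a coronary procedure decided before treatment starts counts as a primary event. With 0.5 to 2 points pre-planned and equal between arms, power is about 78% to 72% if they are part of the 21%, or about 79% to 76% if they are added to it. This rests on the plan's own inputs, on the 12-month rate although the composite is counted over treatment and follow-up, and on an assumed share that the article does not give. The bias route is a possibility without a known direction or size. The change is worth making because it is cheap and concerns the primary endpoint of an open-label cluster trial with no spare power.

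**What to change.** - Add to the Exclusion criteria: coronary revascularization planned or scheduled at enrolment. If the sponsor prefers not to exclude these patients, record the plan at baseline as a yes/no item.
- In Outcome measures, and to match in the Abstract and the Fig. 2 footnote, define the component as revascularization not planned at enrolment.
- Give the endpoint committee the baseline record of planned procedures so that it can apply the rule while blinded.
- Report all revascularizations, planned or not, as a supportive analysis.

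A further restriction to clinically driven procedures is a separate and debatable choice, and this point does not need it.

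Cost: one amendment with one criterion and one definition, one screening item, a slightly smaller eligible pool and slightly fewer counted events. The events given up are procedures whose planning GXNT could not have influenced.

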**Discussion:**

This trial aims to determine whether the addition of GXNT will further improve prognosis without increasing bleeding risk for patients with coronary artery disease who have switched from DAPT to aspirin alone after PCI. Completion of this clinical trial might provide a novel, promising, and safer alternative to P2Y12 inhibitors for prolonged antiplatelet therapy in post-PCI patients.

**Trial registration:**

Chinese Clinical Trial Registry, ChiCTR-IIR-17010688. Registered on 20 February 2017.

**Electronic supplementary material:**

The online version of this article (10.1186/s13063-017-2373-x) contains supplementary material, which is available to authorized users.

## Background

Millions of patients worldwide receive percutaneous coronary intervention (PCI) for treatment of coronary artery disease [1, 2], and treatment with dual antiplatelet therapy (DAPT) for 12 months after PCI has been considered standard care for preventing stent thrombosis and major adverse cardiovascular events (MACEs). Concerning the possibility of late or very late stent thrombosis, which is frequently associated with myocardial infarction, and may be fatal [3], researchers have conducted plenty of studies to explore the benefits and risks of prolonged (>12 month) DAPT [4–9]. Among those, the DAPT trial is the largest and sufficiently powered trial, and demonstrated that, compared with 12 months’ DAPT, an additional 18 months treatment with DAPT  further reduced the risk of stent thrombosis (hazard ratio 0.29, 95% confidence interval 0.17 to 0.48, *p* < 0.001) and MACE rate (hazard ratio 0.71, 95% confidence interval 0.59 to 0.85, *p* < 0.001), establishing the antithrombotic benefits of extended DAPT (>12 months) in post-PCI patients [9]. Later, a systematic review comparing extended DAPT (>12 months) with standard 12 month therapy also confirmed the benefits of extended DAPT, demonstrating that extended DAPT significantly reduced the risk of myocardial infarction (0.53, 95% confidence interval: 0.42 to 0.66) and stent thrombosis (0.33, 95% confidence interval: 0.21 to 0.51) [10]. However, all the antithrombotic benefits of extended DAPT are accompanied by increased bleeding risk, which has raised broad concerns. For example, in the DAPT trial [9], researchers found that 30 months of DAPT led to a 0.9% absolute increase in moderate to severe bleeding risk and a risk–benefit analysis showed that prolonged DAPT, annually, resulted in three fewer stent thromboses and six fewer myocardial infarctions at the cost of five more major bleeds per 1,000 patients. Notably, a recently published meta-analysis of 12 trials, comprising over 34,000 patients receiving different durations of DAPT, revealed that bleeding was an independent predictor of 1-year mortality and that longer duration of DAPT was associated with more bleeding-related deaths [11]. Besides, coronary artery disease itself is an exceedingly costly disease, costing a total of $316.6 billion annually in the USA [1], and prolonged application of the P2Y12 inhibitors will definitely add to the economic burden of both the nation and individuals. Thus, it is urgent to find an alternative drug that is as effective, but safer and more economic than P2Y12 inhibitors.

Traditional Chinese medicine has been used to treat coronary artery disease for quite a long time and is receiving increasing popularity worldwide for its efficacy and low cost [12, 13]. Guanxinning tablet (GXNT) is a traditional Chinese patent medicine and has been approved for marketing by the China Food and Drug Administration. It is developed, for convenience and better compliance, from the widely used Guanxinning injection, whose efficacy in reducing angina attacks and alleviating ST segment depression in the electrocardiogram has been broadly recognized and proved. Results of a meta-analysis involving 6064 patients with angina comparing Guanxinning injection versus control treatments (mainly nitroglycerin and other forms of traditional Chinese medicine), Guanxinning injection plus conventional treatment versus conventional treatment alone, and Guanxinning injection in combination with other forms of traditional Chinese medicine plus conventional treatment versus conventional treatment showed that Guanxinning injection was more effective than all controls in improving angina symptom and alleviating ST segment depression [14]. Guanxinning tablet, usually prescribed as an additional medicine to guideline-recommended standard medical treatment in China, comprises extracts from two well-established Chinese herbal medicines: Danshen (*Salvia miltiorrhiza*) and Chuanxiong (ligustrazine, *Ligustium Wallichii Franch*). Danshen, with tanshinones and phenolic acids as its main active compounds [15], has long been widely used for the prevention and treatment of cardiovascular diseases. An emerging experimental study and clinical trials demonstrated that Danshen and its active compounds could prevent atherosclerosis by inhibiting platelet aggregation, decreasing low-density lipoprotein oxidation, preventing monocyte adhesion to endothelium, and impeding smooth muscle cell migration and proliferation, macrophage cholesterol accumulation, and proinflammatory cytokine production [16, 17]. Chuanxiong, also a commonly used Chinese herbal medicine, together with its active compounds tetramethylpyrazine and ferulic acid could inhibit platelet aggregation and thrombosis [18, 19]. Moreover, preclinical studies indicated that GXNT is effective in inhibiting platelet aggregation, decreasing blood viscosity, and scavenging free radicals, which are all key pro-thrombotic factors [20]. Notably, no adverse events have been reported during the daily use of GXNT. Thus, it appears that GXNT is safe and effective, and may be a promising alternative to P2Y12 inhibitor for prolonged antiplatelet therapy in patients undergoing PCI. However, currently there is no adequately powered study assessing the safety and long-term efficacy of GXNT on clinically relevant outcomes for post-PCI patients.

Therefore, we designed this multicenter cluster randomized controlled trial to assess the long-term benefits, safety, and cost-effectiveness of GXNT for patients who switch from DAPT to aspirin alone after PCI.

## Methods

### Objectives and design

This study is a prospective, multicenter cluster randomized controlled trial aiming to explore whether the addition of GXNT to conventional treatment, including aspirin, will decrease MACEs without increasing bleeding risk for post-PCI patients who switch to aspirin monotherapy after the standard 12 months DAPT. An economic evaluation with 360 participants will be carried out alongside this trial in six of the 36 centers to assess the long-term cost-effectiveness of GXNT. The selection of the six centers takes both area and hospital type into account; three centers in Beijing and three centers in Hangzhou will be chosen. This study follows the international recommendations for interventional trials [21]. (See the SPIRIT checklist in Additional file 1.)

### Inclusion criteria

To be eligible to participate in the trial, patients should:Be currently stable (without angina or with stable angina, defined as persistent and reproducible chest discomfort caused by myocardial ischemia and precipitated by a physical exertion that dissipates upon cessation of such an activity, within the last 3 months before screening) and have received standard DAPT (aspirin plus clopidogrel or prasugrel or ticagrelor) for at least 12 months after PCIHave switched from DAPT to aspirin monotherapy for at least one monthBe diagnosed with the blood stasis pattern of traditional Chinese medicine, which is the most common traditional Chinese medicine syndrome of coronary artery disease; patients with any one of the following signs will be diagnosed as having the blood stasis pattern:dark purple or dark red tongue, or petechia or ecchymosisbluish-purple or dark color of the lipsvaricosity or abnormal telangiectasia of the sublingual veins [22]Be between 18 and 80 years of ageProvide written informed consent.

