### Interventions

All recruited patients will continue to receive aspirin (100 mg once daily) and other conventional treatment including lipid-reducing, antihypertensive, or antidiabetic therapy [23]. Patients recruited from hospitals in the treatment arm will additionally receive GXNT (0.38 g/tablet, China State Food and Drug Administration approval number Z20150028) four tablets each time, three times daily for the first 6 months, and reduce to four tablets each time, twice daily for another 6 months, whereas patients from the controlled hospitals will only receive conventional treatment. At 12 months, patients in the treatment arm will stop GXNT treatment, and then all participants in both the treatment and control arm will continue aspirin monotherapy and other conventional treatment for another 12 months, until month 24. Any kind of other traditional Chinese medicine, including Guanxinning injection, is not allowed for all participants during the whole trial period.

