Data analysis will be conducted by Nanjing Medical University. All analyses will be performed on the individual level with adjustment for clustering and all available data from the dropouts will be included in the analysis up to the time of dropout where possible. All statistical hypothesis tests will be two-tailed and performed at a 5% significance level. Continuous variables will be presented as means and standard deviation, median or interquartile range. Categorical variables will be expressed as frequencies and percentages. Normality of relevant data will be examined using the Shapiro–Wilk test. Cluster-adjusted baseline differences between arms will be analyzed using the independent Student’s *t* test or the Mann–Whitney test for continuous variables and the Pearson *χ*^2^ test for categorical variables. All outcome measures, including the primary outcome measure, will be analyzed using a generalized linear mixed-effect model with the fixed effect being the intervention and the random effect being hospitals, to account for the potential correlation of outcomes within each hospital. Moreover, we will calculate the absolute rate reduction with 95% confidence interval as a crude estimate of the rate difference between the treatment and control groups by using the Mantel–Haenszel method. The number needed to treat for the primary outcome measure as the inverted absolute rate reduction will also be calculated. Efficacy outcomes are to be analyzed according to the intention-to-treat principle.

Safety outcomes will be assessed among all randomized patients except those who do not take any study medication or who have no safety records. The safety outcomes will be summarized and analyzed using the approach outlined.

Missing data will be accounted for by the modern imputation methods and all analysis will be conducted using SAS software version 9.4 (SAS Institute, Cary, NC, USA).

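### Open hospital-level allocation and a judgement-based entry sign let case mix differ by arm, and the stated primary model adjusts for neither baseline prognosis nor the randomisation stratum

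*Protocol article*

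**What the plan says.** All references are to the Methods of the protocol article.

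- **Allocation.** Hospitals are stratified by type (Western medical or traditional Chinese medicine), and then "hospitals in each stratification are randomly allocated in a 2:1 ratio by a computer-generated, centrally controlled randomization schedule". This gives 24 GXNT and 12 control hospitals. "All patients from one cluster will receive same intervention".
- **Blinding (Allocation).** "Though the patients and caregivers are not blinded, the outcome assessors and data analysts are to be blinded to treatment allocation". Staff who recruit are not named among those blinded.
- **Recruitment (Settings and recruitment).** "Potential eligible patients will be screened and assessed by trained investigators", who then seek consent. Patients may come from wards, clinics, advertising, social media or a PCI database. Each hospital is expected to contribute 100.
- **Interventions.** "Patients recruited from hospitals in the treatment arm will additionally receive GXNT".
- **Inclusion criteria.** The blood stasis pattern is required: "patients with any one of the following signs will be diagnosed as having the blood stasis pattern". The signs are the colour or appearance of the tongue, lips or sublingual veins.
- **Analysis (Sample size and data analysis).** All outcomes, including the primary, use a generalized linear mixed-effect model "with the fixed effect being the intervention and the random effect being hospitals". Baseline variables are compared between arms with cluster-adjusted tests. Neither they nor hospital type enter the stated model.

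**The concern.** Randomising hospitals makes the hospitals comparable on average. It makes the patients comparable only if who is enrolled does not depend on the hospital's arm. With one arm per hospital and open treatment, anyone who knows the hospital's arm knows the treatment of the next recruit. A visual sign leaves room for judgement at the margin of eligibility, and patients deciding on consent may also respond to what their hospital offers.

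A systematic difference in case mix of this kind does not shrink as patients are added. The random hospital effect widens the standard error for clustering but does not move the estimate. Intention-to-treat analysis and blinded endpoint adjudication protect the handling and classification of patients already enrolled, not the selection of who is enrolled. Covariate adjustment is the one analytic tool that can remove the recorded part of such a difference, and the stated model does not use it. Separately, the randomisation was stratified by hospital type, and the primary analysis would normally reflect that.

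**Working it through.** **1. Reproducing the plan's sample size.** Inputs from Sample size and data analysis: control risk 0.21; a 21% reduction, read as relative, so GXNT risk 0.21 × 0.79 = 0.1659 (difference 0.0441); two-sided alpha 0.05; power 0.80; ratio 2:1; ICC 0.002; 90 patients per hospital.

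- Pooled risk = (0.21 + 2 × 0.1659)/3 = 0.1806.
- Controls = [1.96 × √(1.5 × 0.1806 × 0.8194) + 0.842 × √(0.21 × 0.79 + 0.1659 × 0.8341/2)]² / 0.0441² = 911.6, so 912; total 3 × 912 = 2736.
- Design effect = 1 + 89 × 0.002 = 1.178; 2736 × 1.178 = 3223.
- Control hospitals = 912 × 1.178/90 = 11.94, so 12. With 24 GXNT hospitals: 36 × 90 = 3240.

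The stated 3240 patients and 36 hospitals are reproduced, so the same inputs can be used for the bias check.

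**2. False benefit when GXNT does nothing.** Assumptions, not in the document: a round event risk of 0.20, and GXNT recruits with a true baseline risk lower by a shift s. Evaluable patients are 24 × 90 = 2160 and 12 × 90 = 1080.

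- SE = √[1.178 × 0.20 × 0.80 × (1/2160 + 1/1080)] = 0.0162.
- Chance of a significant result favouring GXNT = P(Z > 1.96 − s/SE).

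| Assumed shift s | s/SE | Chance of false benefit |
|---|---|---|
| 0 | 0 | 2.5% |
| 1 point | 0.618 | 9.0% |
| 2 points | 1.236 | 23.5% |

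Working instead from the plan's 21% control risk, a 5% relative shift (21.0% v 19.95%) gives 9.4%, and a 10% relative shift (21.0% v 18.9%) gives 25.2%.

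**3. The opposite shift.** Suppose GXNT has its planned effect but its recruits carry a risk 1 or 2 points higher. Here SE = √{1.178 × [0.21 × 0.79/1080 + p(1 − p)/2160]}, and power = P(Z < difference/SE − 1.96).

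| GXNT risk p | Difference | SE | Power |
|---|---|---|---|
| 0.1659 (no shift) | 0.0441 | 0.01601 | 79% |
| 0.1759 | 0.0341 | 0.01612 | 56% |
| 0.1859 | 0.0241 | 0.01623 | 32% |

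(The no-shift figure uses unpooled variances. The pooled formula gives 80.2%.)

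**4. What adjustment can do.** This was simulated with 4000 trials per scenario, no drug effect, a fully recorded baseline marker that doubles risk, and a cluster-level t test standing in for the mixed model.

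| Marker prevalence, control v GXNT | False benefit, unadjusted | False benefit, adjusted |
|---|---|---|
| 50% v 50% | 2.5% | 2.5% |
| 50% v 45% | 7.2% | 3.3% |
| 50% v 40% | 13.7% | 2.8% |
| 50% v 35% | 24.2% | 2.5% |

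Adjustment restores roughly the nominal rate, but only because the marker is recorded and is the only thing that differs.

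**The case against.** **The order of allocation and recruitment is not stated.** A reader might infer that the Interventions wording proves recruiters know the arm before they screen. It does not. That sentence says who receives GXNT and fits either order, and the Allocation section, which speaks of hospitals together with their patients, fixes no order either. Arm first is the natural reading, but it remains a reading. This part of the objection stands.

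**The direction is unknown.** A reader might infer that GXNT hospitals would admit milder patients and so favour the drug. Nothing in the article links a borderline tongue or lip colour to lower risk of the primary outcome. Staff could as easily steer sicker patients towards GXNT, and control hospitals have the same target of 100 patients. This also stands.

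**The shifts are assumed.** They are averages over all GXNT recruits. If one recruit in five were an extra borderline case, a 2-point average shift would need those cases to be 10 points lower in risk. A 3-point shift (45.8% by the same formula) would need 15 points, about 5% against 20%, so that figure deserves no weight.

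**A condensed article may omit recruitment detail.** Consecutive enrolment, screening logs and the timing of arm release may sit in the full protocol, and their absence here is not a fault. The same defence does not cover the model. An unseen analysis plan might add adjusted analyses, but the article states what the primary model contains, and that is content rather than silence.

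**Existing safeguards.** Trained investigators, several more objective entry criteria and the baseline comparison all help. The baseline tests could reveal a recorded imbalance, but the stated plan does nothing with the result.

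**Conclusion.** The point holds as a weakness in the stated analysis, made relevant by the design. Open allocation of whole hospitals and a judgement-based sign mean that enrolled patients could differ by arm, and the primary model would not correct even the recorded part of that difference. It also ignores the stratum used in randomisation.

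Under assumed shifts of 1 or 2 points, about a quarter to a half of the planned 4.4-point effect, the chance of a false benefit rises from 2.5% to about 9% or 23%. Shifts the other way reduce power to about 56% or 32%. These figures show how sensitive the comparison is. They are not estimates of what will happen, and they rest on the plan's ICC, cluster size and event risk together with the assumed shifts. The documents do not support a claim that bias has occurred or that it favours GXNT.

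**What to change.** In Sample size and data analysis, specify the primary mixed model with these fixed effects: intervention, hospital type (the randomisation stratum), and a short list of baseline prognostic factors already collected, for example age, with the others chosen and fixed before unblinding. Keep hospital as the random effect. Keep the model with intervention alone as a sensitivity analysis. State that baseline significance tests will not be used to select covariates.

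Add to the limitations in the Discussion that adjustment removes only recorded imbalance, so some recruitment bias may remain.

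The analysis change costs wording only and needs no new data or patients. Where a hospital's arm has not yet been released, identifying candidates before release is desirable if feasible. It is not clearly cheap: the signs must be examined in person, eligibility changes with time (three months of stability, at least one month on aspirin alone), and a fixed list sits awkwardly with recruitment by advertising. It should therefore be an option, and the model change should not wait for it.
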